### Data collection and management

Data collection and follow-up will be given in line with Table 1 and Fig. 1.

**Table 1 Tab1:** Flow chart of the study outlining follow-up visits and assessments at each visit

	Screening 1 (part 1)	Screening 2 (part 2)	Treatment initiation or referral to standard treatment (physician)	Treatment follow-up (4 weeks after initiation)	Treatment follow-up (8 weeks after initiation)	Treatment follow-up (12 weeks after initiation)	Effect assessment (12 weeks after completion)	Annual follow-up
Acceptable time shift (days)				± 7	± 7	± 7	± 14	± 60
Physician assessment			X				X	X
Research nurse assessment	X	X					X	X
- Informed consent	X							
- Eligibility assessment	X	X	X					
- Follow-up by staff delivering treatment and providing information (several times weekly)			X	X	X	X		
- Clinical assessment	X	X	^b^	^b^	^b^	^b^		X
- Counselling on prevention			X	X	X	X	X	X
Elastography^a^		X					(X)	X
Lab tests								
- Viral testing	X						X	X
Full blood count and transaminases	X			^b^	^b^	^b^	X	X
HSCL-10 (mental health)	X						X	X
FAS (fatigue symptoms)	X						X	X
EQ-5D-5 L (quality of life)	X						X	X
Infection risk behaviour	X						X	X
Substance use patterns	X						X	X
HCV genotyping and viral load	X						X	X

^**a**^Elastography after treatment will be assessed in Bergen and not in Stavanger due to elastography availability only in hospital clinic and not outpatient clinic

^b^Additional tests will be taken on clinical indication

**Fig. 1 Fig1:**
[figure not shown]
Overview of follow-up for the study * The arrows are indications of when the various measured are timed

The blood samples for the primary outcome measures will be collected at the OAT/PWID clinics for participants randomised to integrated care and at the hospital outpatient clinic for the participants randomised to standard care. However, for patients who do not come for assessment at the hospital clinic 12 weeks after treatment, efforts will be made to collect these blood samples at the OAT/PWID clinic. For the remaining outcome measures, these will be measured at the OAT/PWID clinics by research nurses through a structured interview for both participants randomised to standard and integrated treatment.

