### Interventions

Participants randomised to standard care are first assessed and diagnosed at the integrated care clinics for PWID by nurse and physician and when found in need of treatment, are referred to a hospital clinic for further assessment and treatment. The standard care generally involves being referred to the medical outpatient clinic. The clinic will send a letter informing on time of appointment usually some weeks later and could involve some additional blood samples and imaging before initiating DAA treatment. Subsequently, an electronic prescription is given in a consultation where treatment is initiated. The medications given are in principle equivalent in the two trial arms. Most will receive medication combinations of either elbasvir/grazoprevir 50/100 mg or sofosbuvir/ledipasvir 400/90 mg (for genotype 1 and 4) or sofosbuvir/velpatasvir 400/100 mg (for genotype 2 and 3) – sometimes also in combination with voxilaprevir 100 mg or ribavirin 200 mg due to specific clinical indications. Glecaprevir/pibrentasvir 100/40 mg may also be used in special cases. Patients are generally given follow-up consultations every 4 weeks during treatment and a post-treatment assessment 12 weeks after completed treatment. Typically, this involves a total of 4–5 consultation visits at the hospital.

Participants randomised to integrated treatment are given integrated assessment and treatment at the clinics for PWID (by nurse and physician). For those found to be in need of treatment, medications are made available by a nurse that gives follow-up for OAT or low-threshold care for PWID. Follow-up during treatment is given in parallel with delivery of OAT treatment and other care. At 12 weeks post treatment, a research nurse takes blood samples to assess the treatment effect.

The differences between the delivery platforms in the two trial arms involve the following main aspects:

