
### Sample size

We expect higher rates of treatment success in the intervention arm receiving integrated treatment compared to the standard arm. The power calculation is based on the following assumptions:
The power is set at 90% with a two-sided alpha (α) error of 5%.Comparison of SVR at 12 weeks.Up to 33% lost to follow-up at 12 weeks after treatment.Equal proportions between the groups, 30% higher rates of successfully cured in integrated compared to standard treatment (e.g. 50% in the standard arm and 80% in the intervention arm).Statistical power calculations in Stata.

Based on these assumptions, 87 persons are required in intervention arm and 87 persons in the control arm. Reducing the differences in rates of successfully cured to 25% while reducing power to 80%, 99 persons in each arm would be required (or 66 persons if assuming no lost-to-follow-up).

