### Allocation and blinding

We will use block randomisation with a 1:1 ratio using blocks of 10 to ensure relatively similar distribution between both arms throughout different time periods of the trial. Randomisation will be electronically registered. The randomisation will be stratified by site/county (site 1: Bergen/Hordaland and site 2: Stavanger/ Rogaland).

Even though complete blinding is regarded as difficult and would probably come at a cost of reduction in external validity [21], there will be some degree of blinding/masking. Randomisation will be disclosed to physician and other health care staff providing treatment and follow-up for PWID, but not to research nurses conducting data collection for outcomes. Patients will be informed of which intervention arm they are randomised to and the form of follow-up they will receive, but not on other follow-up alternatives they do not receive and what the hypotheses for the study are.

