Our trial involves some limitations and several strengths. For the trial it is difficult to ensure complete blinding, however, we will aim for blinding of data collectors and some degree of blinding for participants. The study is also funded from public sources ensuring independency. We also have a biological primary outcome. Thus, substantial information biases are considered unlikely. The study is individually randomised minimizing potential confounding. The study population of PWID will include a large proportion struggling to obtain standard care. This will not be applicable to all groups of people with substance use disorders. For people with substance use disorders with higher levels of functioning and less need for regular treatment follow-up, the need for treatment integration might not be as relevant. The study setting is also very suitable to test out treatment integration. The time prior to change in the national guidelines for treatment of HCV made it necessary for some people to delay HCV treatment initiation. This might impact negatively on the treatment outcomes, but probably is balanced between the arms. Further, most of the participants will be treated after the guideline changes where treatment is now available independent of stage of liver fibrosis. Subsequently, we assume that this effect will not be substantial. The study might be well suited to assess some biological effects of HCV infection such as to which extent HCV contributes to fatigue, reduced quality of life, occurrence of mental disorders and continued drug use. The study size should be sufficient to answer the primary objectives with high precision and is assumed to have adequate precision also for secondary objectives. In terms of safety, the frequent follow-up of PWID could improve detection of potential adverse effects of the applied medications. One can see trials on a continuity from efficacy trials optimising internal validity through homogeneous population to effectiveness trials optimising external validity with a more heterogeneous population. This trial is tending towards the effectiveness side of the spectrum. An alternative design could have been a stepped-wedge trial which could have required slightly smaller sample sizes and would also be well opted to measure effectiveness of integrated treatment. However, we expect to have enough participants to meet the sample size requirements. On the other side, stepped-wedged trials generally take longer time to conduct due to the time delay. In addition, our more conventional trial design is less vulnerable to confounding from time trends.

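### The primary SVR sample is drawn at a different site in each arm, so the access barriers under test can also influence who has an SVR result

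*Protocol article*

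**What the plan says.** Under Data collection and management (text below Fig. 1), the blood samples for the primary outcome are "collected at the OAT/PWID clinics for participants randomised to integrated care and at the hospital outpatient clinic for the participants randomised to standard care". The next sentence adds a fallback: if a patient does not come to the hospital assessment, efforts will be made to take the sample at the OAT/PWID clinic. No number of attempts or start time is given.

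For the integrated arm, Interventions says: "At 12 weeks post treatment, a research nurse takes blood samples to assess the treatment effect". All other outcomes have one site in both arms: "For the remaining outcome measures, these will be measured at the OAT/PWID clinics by research nurses through a structured interview".

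Outcomes defines SVR as undetectable HCV RNA at 12 weeks after completed treatment, with a range of 10 to 14 weeks. Table 1 gives the matching tolerance of ±14 days for the effect assessment. It lists research-nurse assessment and viral testing at that visit without distinguishing the arms.

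Interventions names travel of 1 to about 25 km, fixed appointments and unfamiliar clinicians as features of standard care that integrated care generally avoids. Sample size allows for up to 33% loss, not split by arm. Analyses and statistical methods leaves the handling of missing data to a later detailed plan.

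**The concern.** The trial asks whether removing travel and appointment barriers improves treatment uptake and cure. Those barriers belong in the treatment pathway of the standard arm. With the sampling site fixed by arm, they also stand between a standard-arm participant and the measurement of the outcome. Someone who was treated and cured but does not attend the hospital 12 weeks later may have no SVR result. The same person in the integrated arm would be sampled at a clinic they already visit.

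The fallback reduces this but does not make the arms equal. It is best-effort, and it starts only after a hospital assessment has been missed, so part of the four-week window may already be used. An effect on attendance for the test could then be read as an effect on cure. SVR is a primary outcome and the one on which the sample size rests.

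**Working it through.** **1. The plan's own figure.** Inputs from Sample size: "Comparison of SVR at 12 weeks", "50% in the standard arm and 80% in the intervention arm", 90% power, two-sided 5%, 33% loss. The continuity-corrected two-proportion formula gives 58 per arm, and 58/(1 − 0.33) = 86.6, so 87, as stated. The alternative (50% v 75%, 80% power) gives 66, and 66/0.67 = 98.5, so 99, also as stated. The 33% was therefore applied to both arms alike. The number 87 is not in dispute and is used below.

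**2. Missing counted as failure, equal true cure.** Let c be the true cure proportion, the same in both arms, and let m be the proportion with an SVR result, unrelated to cure. The observed SVR is c × m, and the spurious difference is c × (m_int − m_std). The chance of a significant result in favour of integrated care is taken from the two-proportion z-test (two-sided 5%, n = 87 per arm):

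Φ[(d − 1.96·SE₀)/SE₁], with d the difference in observed SVR, SE₀ the pooled and SE₁ the unpooled standard error.

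The values of m are assumptions, since the protocol gives none by arm. The 67% borrows the overall loss ceiling and places all of it in the standard arm, so it is an unfavourable case.

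| Measured, integrated v standard | Cure 75%: observed SVR, gap | False significance | Cure 80%: observed SVR, gap | False significance |
|---|---|---|---|---|
| 67% v 67% | 50.3% v 50.3%, 0 | 2.5% | 53.6% v 53.6%, 0 | 2.5% |
| 95% v 90% | 71.3% v 67.5%, 3.8 points | 8% | 76.0% v 72.0%, 4.0 points | 9% |
| 95% v 80% | 71.3% v 60.0%, 11.3 points | 34% | 76.0% v 64.0%, 12.0 points | 41% |
| 95% v 67% | 71.3% v 50.3%, 21.0 points | 81% | 76.0% v 53.6%, 22.4 points | 88% |

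The difference planned for is 30 points. The correct false-positive rate in this direction is 2.5%.

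**3. Complete cases, equal true cure.** If measurement is unrelated to cure within each arm, both arms estimate c and there is no bias, whatever the values of m. Now suppose uncured standard-arm participants are r times as likely to be measured as cured ones, while measurement in the integrated arm is unrelated to cure. The standard arm then shows c/(c + (1 − c)·r):

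- c = 0.80, r = 0.7: 0.80/(0.80 + 0.14) = 0.851, a bias of 5 points against integrated care.
- c = 0.80, r = 0.5: 0.80/(0.80 + 0.10) = 0.889, a bias of 9 points against.
- c = 0.50, r = 0.7 and 0.5: 0.588 and 0.667, a bias of 9 and 17 points against.

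The same collection scheme can thus bias the comparison in either direction, depending on a rule that this document does not set.

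**The case against.** The fallback has real substance. Research nurses see both arms at the OAT/PWID clinics for every other 12-week outcome, inclusion requires weekly follow-up at an included clinic, and OAT patients attend nearly daily. A missed hospital sample may therefore often be recovered within the window. Nothing in the article shows that it will not be, and nothing implies 95% v 67%. This stands, and it is why the point is a risk whose size may be as small as the 4-point row. It does not remove the risk, because the fallback has no stated rule and comes second in one arm only.

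The missing-data rule may also deal with part of the problem. That stands too: the protocol does not adopt missing-equals-failure. But any imputation for SVR rests on assumptions that the data cannot test, whereas equal collection reduces the need for them.

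Two stronger readings are tempting. The first is that the scheme unblinds the outcome assessment. Allocation is to be disclosed to treating staff "but not to research nurses conducting data collection for outcomes", and a nurse might guess the arm from whose blood is drawn. However, the fallback also brings standard-arm draws to the same clinic, the article claims only partial masking, and SVR is a laboratory HCV RNA result that a nurse's guess does not alter. The second is that the Discussion's statement "Thus, substantial information biases are considered unlikely" is thereby refuted. That statement concerns error in what is measured and leans on a biological outcome. The issue here is who gets measured, which the statement does not address.

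**Conclusion.** The point holds as a risk of differential ascertainment of a primary outcome, built in by an arm-specific sampling site that the trial does not need. It is not shown that results will be missing more often in the standard arm, nor that the trial will favour integrated care.

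With missing counted as failure, equal cure of 75–80% and 87 per arm, the possible distortion runs from none (equal ascertainment) through about 4 points (fallback largely successful) to 21–22 points (the whole loss ceiling in one arm). The top figure should not be read as a forecast. With complete cases the bias is nil or runs the other way. The claim rests on the stated sampling sites and on the assumed proportions measured, not on any observed imbalance. The sample size itself is reproduced and is unaffected.

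**What to change.** In both arms, draw the outcome HCV RNA sample at the OAT/PWID clinic, at the 12-week effect-assessment visit that research nurses already hold there, within the same 10 to 14 week window. Let a hospital sample count only as back-up, under one written rule that applies to both arms. Report the proportion with an SVR result by arm and by sampling site.

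Do not widen the definition by accepting any late undetectable sample as SVR. That would be one-sided: it admits late successes but has no rule for a late detectable result, which may be reinfection.

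The cost is a change of protocol wording and possibly one duplicate blood draw for standard-arm participants who also attend the hospital. No new visit or staff is needed, and the hospital follow-up in standard care stays as it is.

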### Analyses and statistical methods

A detailed plan for analysis will be developed before data export and analysis. We will in this section outline some of the principles which will be used to guide decisions during data analysis. Analysis methods will follow the CONSORT and SPIRIT guidelines as far as possible [22–24]. All tests will be two-sided. Descriptive results and efficacy estimates will be presented with 95% confidence intervals. The statistical significance is set at *p* < 0.05. Potential confounders may be considered for adjustment if they are imbalanced at baseline (with assumed meaningful differences). Missing data will be considered, and appropriate imputations based on pre-defined assumptions will be done when necessary (as described in detailed plan of analysis). Categorical variables will be summarized as percentages and continuous variables as medians with interquartile ranges or means with standard deviation for variables with a Gaussian distribution. The main outcomes will be analysed with time-to-event analysis (Cox regression and Kaplan-Meier plots) and generalised linear models/logistic regression. A separate health economic evaluation will assess the incremental cost-effectiveness ratio of the intervention arm compared to the control arm. A Markov model will be used, and the analysis will be exhibited in TreeAge. Results will be presented as cost per QALYs of integrated versus standard HCV care.

## Discussion

The research project will improve knowledge on the impact on health care organisation and structure on patient outcomes. We will assess a platform aiming for easier access to treatment of HCV among PWID who have been difficult to reach with ordinary health services. Integrated treatment models may be an opportunity to increase adherence to HCV treatment and evaluate collaborative care in light of access to direct acting antiviral medications. The treatment platform could reduce the burden of HCV among this patient population and could contribute to HCV elimination. We will test this with a randomised controlled trial done in parallel with an observational study assessing HCV reinfections, other infections including HIV, and liver disease severity.

Our trial involves some limitations and several strengths. For the trial it is difficult to ensure complete blinding, however, we will aim for blinding of data collectors and some degree of blinding for participants. The study is also funded from public sources ensuring independency. We also have a biological primary outcome. Thus, substantial information biases are considered unlikely. The study is individually randomised minimizing potential confounding. The study population of PWID will include a large proportion struggling to obtain standard care. This will not be applicable to all groups of people with substance use disorders. For people with substance use disorders with higher levels of functioning and less need for regular treatment follow-up, the need for treatment integration might not be as relevant. The study setting is also very suitable to test out treatment integration. The time prior to change in the national guidelines for treatment of HCV made it necessary for some people to delay HCV treatment initiation. This might impact negatively on the treatment outcomes, but probably is balanced between the arms. Further, most of the participants will be treated after the guideline changes where treatment is now available independent of stage of liver fibrosis. Subsequently, we assume that this effect will not be substantial. The study might be well suited to assess some biological effects of HCV infection such as to which extent HCV contributes to fatigue, reduced quality of life, occurrence of mental disorders and continued drug use. The study size should be sufficient to answer the primary objectives with high precision and is assumed to have adequate precision also for secondary objectives. In terms of safety, the frequent follow-up of PWID could improve detection of potential adverse effects of the applied medications. One can see trials on a continuity from efficacy trials optimising internal validity through homogeneous population to effectiveness trials optimising external validity with a more heterogeneous population. This trial is tending towards the effectiveness side of the spectrum. An alternative design could have been a stepped-wedge trial which could have required slightly smaller sample sizes and would also be well opted to measure effectiveness of integrated treatment. However, we expect to have enough participants to meet the sample size requirements. On the other side, stepped-wedged trials generally take longer time to conduct due to the time delay. In addition, our more conventional trial design is less vulnerable to confounding from time trends.

Our assessment will also inform future health policy on efficiency by using standard methods of cost-effectiveness analysis taking both the expected effectiveness and provider costs of the intervention into consideration. Even though there is evidence on the cost-effectiveness of standard DAA in HCV treatment regimens; there is limited evidence for the cost-effectiveness of alternative scale-up scenarios taking the complex behavior of PWID into account [27].

If the integrated treatment model for HCV in clinics for PWID compared to standard care is found to be safe and efficacious in terms of increasing access and improving treatment outcomes, this model could be considered for further scale-up.

## Data Availability

Trial outcome data is not yet available.

## Abbreviations

DAA: Direct-acting antiviral treatment
HCV: Hepatitis C virus
OAT: Opioid agonist therapy
PWID: People who inject drugs
QALY: Quality Adjusted Life Year
SAE: Severe adverse effects
SVR: ustained virologic response
